## Abstract

**Background:**

Both physical inactivity and sedentary behavior are considered modifiable risk factors for chronic diseases and all-cause mortality. Adult office-workers spend most of their working day in sedentary behaviors, so they are particularly at high risk of developed chronic diseases (e.g., cardiovascular diseases, metabolic disorders like diabetes mellitus, …). It seems important to promote behavioral changes that could prevent or delay metabolic disease development. Evidence supports the use of exercise programs, however, to date there are several knowledge gaps and inconsistencies in the literature regarding the effects of Combined Training (i.e., aerobic plus resistance training) in sedentary healthy adults. This paper outlines an RCT designed to evaluate the effects of a 16-week combined training program on biochemical and immune markers of metabolic disease, lung function, salivary stress hormones and subjective quality of life (primary outcomes), as well as on body composition and physical fitness (secondary outcomes) in sedentary middle-aged office-workers. Furthermore, we aimed to assess the associations between the changes promoted by the exercise program and the different variables studied.

**Methods and design:**

This is a single-blinded two-arm RCT with parallel groups. A minimum of healthy 40 office-workers aged 40–64 years will be recruited to engage in a 16-week intervention study. After baseline assessments, participants will be randomized to one of the two groups: (1) combined training group or (2) control group. Baseline assessments will be repeated after 8 weeks of intervention (mid-testing) and upon completion of the intervention (post-testing).

**Discussion:**

This RCT involves a multi-disciplinary approach and seems to be a relevant contribution to understanding the potential role of combined training in improving the metabolic profile, lung function, stress, and quality of life in adults. The results can provide important insights for clinical recommendations and for the optimization of strategies to prevent metabolic disorders in adults with sedentary jobs.

**Trial registration:**

This trial is registered with ClinicalTrials.gov (registration number: NCT04868240; date of registration April 30, 2021).

## Introduction

The increased urbanization and technological advancements have been accompanied by a high prevalence of sedentary behaviour (SB) and physical inactivity (PI) worldwide, especially in the workplaces [1, 2]. A recent review found that working adults spent about 60% of their waking time in SB and about 4% of the day in moderate to vigorous physical activity (PA) [3]. When compared to other occupations, office-workers had more time spent on SB and less time spent in light PA, both at work as during the wakeful hours [3]. These behavioural patterns have important implications for health since they are associated with many chronic non-communicable diseases (NCDs) [4–6] and even premature death in adults [5–9]. More specifically, the lack of regular PA and the high prevalence of SB promote visceral fat accumulation and hence an increased chronic low grade inflammation and the onset of metabolic disorders, including metabolic syndrome [10–12] that represents a clustering of risk markers (like abdominal obesity, hyperglycaemia, hypertriglyceridemia, low high-density lipoprotein cholesterol (HDL-C), insulin resistance (IR) and pro-inflammatory status) [13], strong and independent contributors to the development of type 2 diabetes mellitus (T2DM) and cardiovascular diseases [14, 15]. A recent study of 2.497 middle-aged adults [16] showed that for each additional hour daily of SB during waking time, the odds of developing T2DM and metabolic syndrome increased by 22% and 39%, respectively. According to Leong et al. [17], T2DM is preceded by IR years before symptoms arise, and not all individuals with obesity and genetic predisposition develop this disease. Thus, it seems important to identify those at risk for IR and other risk factors (e.g., abdominal obesity, chronic systemic inflammation) at an early stage [18]. In addition to the negative impact on metabolic health, an inactive lifestyle also accelerates the age-associated decline in lung function [19–21]. In turn, reduced lung function has been associated with an increase of chronic non-communicable diseases (NCDs) and death [19, 22]. The mechanisms through which high levels of SB may affect lung function are not well understood, however, some studies speculate that inflammation may be a biological link [20]. Stress and health-related quality of life (HRQoL) are also important components of health [23] and studies showed that, in the work context, the time in occupational sitting can be associated with increased stress (i.e., salivary cortisol (s-COR) levels) [24–26].

Considering the levels of sedentariness and physical inactivity in office workers, and its negative impact on health, it seems vital to promote behavioural changes that could prevent or delay metabolic disease development, as well as improve lung function, stress, and HRQoL. Regular exercise has been proposed for the prevention and treatment of many chronic NCDs, including T2DM since it promotes metabolic and immune changes [11, 27, 28]. Its protective health effects can be attributed to the anti-inflammatory effects of exercise, mediated by protection against visceral fat accumulation, increasing the secretion of anti-inflammatory cytokines, such as interleukin (IL)-10, IL-1ra and serum adiponectin levels, and decreasing the pro-inflammatory cytokines like tumor necrosis factor-alpha (TNF-α), IL-1β, IL-6 and serum leptin levels [11, 27, 29]. Although moderate evidence supports the use of exercise programs to prevent or reverse metabolic disorders, to date, there are several knowledge gaps and inconsistencies in the literature regarding the optimal dose and type of exercise [30–32]. Aerobic exercise (AE) has been deemed effective to improve metabolic profile (e.g., reduce IR and increase anti-inflammatory effects) [33–35]. Evidence regarding resistance exercise (RE) is not as strong, but besides increasing muscle strength, it can also induce beneficial changes on some metabolic risk factors [36–38]. However, whether a combined training (CT), combining AE and RE, may be more effective and provide an additive effect in promoting a better metabolic profile in sedentary adults remains to be determined. Some studies have demonstrated that CT improves body composition [32, 39–41], inflammatory cytokines [32, 41], IR [39, 41, 42] and other metabolic disease risk factors [32, 39, 40, 43]. However, these studies have had one or more of the following methodological confounds: vast breadth of populations (i.e., elderly) [40, 42], co-morbidities included (i.e., T2DM) [32, 39, 43] which may limit generalizability to the adults that are healthy; and short intervention durations or lack of a control group [39, 41]. Thereby, and according to a recent meta-analysis [31], more studies with CT are required to improve the quality of evidence on this topic. Regarding lung function, cross-sectional studies have shown a positive association between PA levels and lung function among middle-aged adults without a respiratory disease [20, 21], however, causal inferences cannot be made. To our knowledge, the effects of a long-term CT exercise program on the lung function of healthy adults have not been examined, with the published studies focusing on adults with obstructive lung diseases [44]. The effectiveness of a long-term CT program in aspects of stress and HRQoL are also not well established, however, some studies suggest that PA is beneficial on the regulation of stress [24, 25]. The s-COR and alpha-amylase (s-AA) are the proxy markers of the two main stress response systems [45] and could be used to assess the stress levels of worker adults, increasing knowledge on the effects of a CT program on these indicators.

Unfortunately, the high methodological confounds of some of the previous studies and knowledge gaps lead to little evidence regarding the effectiveness of CT to improve the biochemical and immune markers of metabolic disease, lung function, quality of life, and stress in sedentary adult office workers. So, new studies are required to improve the quality of evidence on this topic. This trial aims to analyse the effects of a 16-week CT program on metabolic disease risk markers, including inflammatory cytokine profile, markers of IR (fasting glucose and insulin levels, HOMA-IR), leptin and adiponectin levels (as surrogate markers of adipose tissue dysfunction), lung function, salivary stress hormones and subjective quality of life (primary outcomes), as well as body composition and physical fitness (secondary outcomes), in sedentary middle-aged office workers of both genders. Furthermore, we aimed to assess the associations between the changes promoted by the exercise intervention and the different variables studied.

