#### Primary outcomes

*Biochemical assessment I*: *Fasting blood samples*. Blood collection will be performed in a seated position from the antecubital vein, at rest after a 12-hours overnight fast, and the blood samples will be aliquoted into kEDTA and serum tubes. The participants will be instructed to avoid extreme physical efforts 24 hours before the blood collection. Determination of blood counts will be done immediately after the blood collection, using an automated Coulter Ac•T diff Hematology Analyzer (Beckman Coulter^®^, Inc, USA). Biological samples will be centrifuged at 1500xg for 10-min and plasma and serum samples will be frozen at -80°Celsus (C) for posterior analysis. The levels of insulin, glucose, glycated haemoglobin (HbA1c), total cholesterol, low-density lipoprotein cholesterol (LDL-C), HDL-C, triglycerides, cytokines IL-1β, IL-1ra, IL-6, IL-10, transforming growth factor beta 1 (TGF-β), TNF-α, adiponectin and leptin will be analysed. Fasting glucose, triglycerides and cholesterol levels will be determined by standard enzymatic assays (ABX Pentra, Germany). Insulin, leptin and adiponectin will be analysed by ELISA (R&D Systems, UK). The Homeostatic model assessment (HOMA-IR) will be calculated using the Matthews formula [65]:

$$HOMA-IR=\frac{fasting\;glucose\;[mmol/L]\;x\;fasting\;insulin\;[\mu U/l]}{22.5}$$

Inflammatory cytokines will be analysed by ELISA kits (Thermofisher, UK) according to the manufacturer instructions. All blood collections for the biomarker analysis will be performed in the morning (between 07:30h – 10:30h) by a registered nurse.

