*Biochemical assessment II*: *Saliva samples*. Saliva will be collected through a gold standardized method for biological assays—passive drool—which requires participants to “expel” saliva (let the saliva drop) into polypropylene tubes [66]. The participants will be comfortably seated with their head slightly lowered, allowing spontaneous saliva flow to accumulate in their mouth [67]. Before saliva collection, the participants will be instructed to rinse their mouth for 60 seconds with water to remove any food residues and then wait at least 10 minutes [67, 68] before saliva collection. Moreover, according to procedures in other studies, the participants will be required to avoid vigorous physical exercise 24h before the collection, alcohol for 12 hours, brush teeth or eat a major meal for 60 minutes, and foods with high sugar, acidity, or caffeine immediately before sample collection [67, 68]. After collection, saliva samples will be stored frozen at −20°C until assayed. The saliva samples will be subject to a single freeze-thaw cycle. On the day of the assay, samples will be centrifuged to remove particulate matter, and the salivary levels of cortisol (s-COR), α-amylase (s-AA), immunoglobulin A (s-IgA), and Lysozyme (s-Lys) will be analyzed by commercial kits. S-COR, s-IgA, and s-Lys will be analyzed by ELISA (Salimetrics, USA) and s-AA by a kinetic reaction assay (Salimetrics, USA), according to the manufacturer instructions. All saliva collections for biomarker analysis will always occurred at the same time in the morning to minimize circadian effects (between 09:30h – 10h30).

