*Brachial blood pressure*. The right and left brachial systolic blood pressure (SBP) and diastolic blood pressure (DBP) will be measure using an automated oscillometric cuff (OMRON, HEM 907, Japan). The participant will be comfortably seated, with the legs uncrossed and the back and arm supported, for 3–5 minutes without speaking and/or moving before recording the first measure [69, 70]. Two readings will be taken at intervals of at least 1–2 minutes and the average of those readings will be recorded as the participant’s BP. However, if the values deviate by ≥ 5 mmHg, a third measurement will be performed, and the average of these multiple readings will be used [69, 70]. The participants must avoid caffeine, physical exercise, and smoking for at least 30 minutes prior to measurement [69]. The brachial BP will be assessed in the morning (between 09:00h – 12:00h) and will be performed by a doctor.

*Lung function*. Spirometry will be conducted using the Spiropalm 6MWT (Cosmed, Italy) Spirometer. Participants will perform a maximal inspiratory and expiratory maneuver to achieve the Forced Vital Capacity (FVC), Forced Expiratory Volume in 1 second (FEV_1_), and Peak Expiratory Flow (PEF). Participants’ data will be classified to indicate repeatability. In this sense, the participants will have to complete at least three acceptable FVC maneuvers to be included in the analysis (i.e., the difference between the best two FEV_1_ and FVC values must be within 150 mL) [71, 72]. The best FEV_1_ and best FVC measures of the participants will be recorded and used for data analysis, according to procedures adopted in other studies [20, 21]. Predicted FEV_1_ (FEV_1_% pred), predicted FVC (FVC% pred), and predicted PFE (PFE% pred) will be calculated based on age, stature, ethnicity, and sex using the formulas developed by the Global Lung Function Initiative [73]. The lung function assessment will occur in the morning (between 09:00h – 12:00h) and will be performed by a doctor.

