### Data analysis

Data analyses will be performed using SPSS Statistics version 25.0 (SPSS Inc., IBM Company, Chicago, Illinois, USA). Descriptive statistics (mean ± SD) will be performed for all variables in the analysis. The assumption of normality will be tested using histograms, normal probability plots and Shapiro-Wilk test. Chi-squared test will be performed to analyse sex proportions between groups. Assuming data normality, a two-way analysis of variance (ANOVA) for repeated measures will be applied for intra- and inter-group comparisons. In absence of normality, non-parametric Kruskall-Wallis test will be used. Bonferroni’s *post hoc* test will be performed if significant differences exist (alpha level set at 0.05). The magnitude of the global effect size will be calculated using Cohen’s effect size [104]. The Cohen’s d effect size is categorized according to the following criteria: *d* = < 0.20 (small), 0.21–0.79 (medium) and > 0.80 (large) [104]. The bivariate associations between the changes promoted by the exercise program and the different variables studied will be assessed by Spearman’s rank and Pearson’s coefficients. The strength of the associations will be classified as follows [105]: very high (0.90 < r < 1.00); high (0.70 < r < 0.90); moderate (0.50 < r < 0.70); low (0.30 < r < 0.50); little (0.10 < r < 0.30). Significance level set at *p* ≤ 0.05.

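### Some 30 to 45 measures are all primary, none is ranked first and each is tested at 5%, so a false positive primary result is more likely than not under moderate correlation

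*Protocol article*

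**What the plan says.** The Abstract and the last paragraph of the Introduction label several families as primary. The Introduction names metabolic risk markers (cytokines, insulin resistance markers, leptin, adiponectin), then "lung function, salivary stress hormones and subjective quality of life (primary outcomes), as well as body composition and physical fitness (secondary outcomes". Neither place puts one measure or one time point first.

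The Primary outcomes section and the quality-of-life section after it give the contents:

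- Blood: "The levels of insulin, glucose, glycated haemoglobin (HbA1c), total cholesterol, low-density lipoprotein cholesterol (LDL-C), HDL-C, triglycerides, cytokines IL-1β, IL-1ra, IL-6, IL-10", then TGF-β, "TNF-α, adiponectin and leptin will be analysed". In addition, "The Homeostatic model assessment (HOMA-IR) will be calculated using the Matthews formula".
- Saliva: "the salivary levels of cortisol (s-COR), α-amylase (s-AA), immunoglobulin A (s-IgA), and Lysozyme (s-Lys) will be analyzed by commercial kits".
- Blood pressure: "The right and left brachial systolic blood pressure (SBP) and diastolic blood pressure (DBP".
- Spirometry: FVC, FEV1 and PEF, with percent-predicted versions.
- Questionnaires: WHOQOL-BREF, SWLS, PSS and SF-36.

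The Data analysis section plans a two-way repeated-measures ANOVA with significance at p ≤ 0.05. The Bonferroni post hoc "test will be performed if significant differences exist (alpha level set at 0.05"). The Estimated sample size section gives 20 per group for 95% power at an effect size of 0.30, using one F test at 5%. It does not say for which outcome.

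**The concern.** With many co-equal primaries, each judged at 5%, no single result answers the trial's question. One or two nominally significant primary findings would be expected even from an inert programme, and the plan gives a reader no rule for telling them from real effects. A Bonferroni step that follows a significant ANOVA adjusts the pairwise comparisons within that outcome. It leaves the error rate over the set of outcomes untouched. The stated 95% power belongs to one test at 5%, so it does not carry over if a correction across outcomes is added later.

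The primary set is also not the same everywhere. Blood pressure stands under the Primary outcomes heading but is named in neither the Abstract nor the aims. Salivary IgA and lysozyme are listed as primary measures, while the aims speak only of salivary stress hormones.

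**Working it through.** **1. Count of primary measures**

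| Group | With subscales | Totals or summaries only |
|---|---|---|
| Blood analytes and HOMA-IR | 15 + 1 = 16 | 16 |
| Saliva | 4 | 4 |
| SBP, DBP | 2 | 2 |
| FVC, FEV1, PEF | 3 | 3 |
| WHOQOL-BREF | 4 domains | 1 |
| SWLS | 1 | 1 |
| PSS | 1 | 1 |
| SF-36 | 8 subdomains | 2 |
| **Total** | **39** | **30** |

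Adding a WHOQOL-BREF general score (1), the two SF-36 summaries (2) and three percent-predicted values (3) gives 39 + 6 = 45. Blood counts and separate arms for blood pressure are left out.

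**2. The plan's own sample size**

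Inputs from Estimated sample size: effect size 0.30, N = 40, 5% level, F test. Assumed because not stated: the effect size is Cohen's f for a group-by-time interaction, with m time points and correlation ρ between them.

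λ = f² × N × m / (1 − ρ), with degrees of freedom (m − 1) and (N − 2)(m − 1).

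For m = 2 and ρ = 0.5: λ = 0.09 × 40 × 2 / 0.5 = 14.4, F(1, 38), power 0.959. The smallest even N reaching 95% is 40, so this reading reproduces the stated figure.

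**3. Chance of a false primary result when nothing works**

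One test per outcome at 5%. Expected false positives: 30 × 0.05 = 1.5; 39 × 0.05 = 1.95; 45 × 0.05 = 2.25. Under independence the chance of at least one is 1 − 0.95^k. With correlation, the test statistics are taken as equicorrelated normal; the correlations are assumptions, as the protocol gives none.

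| Measures | Independent | r = 0.3 | r = 0.5 | r = 0.6 | r = 0.7 |
|---|---|---|---|---|---|
| 30 | 79% | 66% | 51% | 42% | 34% |
| 39 | 86% | 74% | 57% | 47% | 37% |

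The chance drops below one half at a uniform correlation just above 0.5 for 30 measures and between 0.55 (52%) and 0.6 (47%) for 39. A more realistic pattern has stronger correlation within a domain than between domains. For 42 measures in 8 blocks the chance is 78% (0.5 within, 0.1 between), 67% (0.7, 0.2) and 57% (0.8, 0.3).

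The ANOVA also yields group, time and interaction tests, so one test per outcome is a low count.

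**4. Cost of correcting across outcomes afterwards**

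Bonferroni over 39: 0.05 / 39 = 0.00128 per test, N = 40, f = 0.30.

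| Time points, ρ | λ | Power at 0.05 | Power at 0.05/39 |
|---|---|---|---|
| 2, 0.3 | 10.3 | 88% | 41% |
| 2, 0.5 | 14.4 | 96% | 62% |
| 2, 0.7 | 24.0 | >99% | 91% |
| 3, 0.5 | 21.6 | 99% | 82% |

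Table 3 has blood and saliva at two time points and spirometry and quality of life at three, so no single row stands for all primaries.

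**The case against.** Several points against the concern have force.

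- **The count is a matter of reading.** A reader might take 39 as a minimum. It is not: the protocol speaks of a final WHOQOL-BREF score and allows the SF-36 domains to be grouped into two summaries, which gives 30. The conclusion survives, because 30 tests still give 51–79% over r = 0.5 to independence.
- **Independence is not credible.** HOMA-IR is computed from glucose and insulin, and lipid fractions, FVC with FEV1, and questionnaire subscales overlap. The 86% is therefore an upper figure for 39 tests and should not be quoted alone. Correlation strong enough to bring the chance below one half would have to hold uniformly across blood, saliva, spirometry and questionnaires, which is implausible.
- **The power loss rests on unstated inputs.** A reader might infer that the trial planned for a 1.2 SD effect (from 20 × d² / 2 = 14.4). The protocol states only 0.30; the rest depends on the assumed time points and correlation.
- **No lead hypothesis is given.** A reader might infer that insulin resistance leads. The Discussion names inflammatory status before it, and the aims put cytokines first. The documents do not rank them.
- **Blood pressure may fit the aims.** The Introduction's list of metabolic risk markers is open-ended, so it does not clearly exclude blood pressure. The Abstract does not name it either.
- **A separate analysis plan could add adjustment, and the sponsor commits to publish whatever the result.** Publication limits selective reporting but not the error rate. The co-equal labels, the 0.05 rule and the role of the Bonferroni step are stated in this document, so the point is not about missing detail.

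**Conclusion.** The point holds. The protocol labels or lists about 30 to 45 measures as primary, ranks none first, tests at p ≤ 0.05 and controls error only within an outcome. With no true effect, 30 to 39 tests give about 1.5 to 2 false positives. The chance of at least one is 79–86% under independence and about 51–74% at assumed correlations of 0.3 to 0.5; it falls below one half only under strong uniform correlation (about 0.6 or more for 39 measures, a little above 0.5 for 30).

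A Bonferroni correction over 39 outcomes would lower power at N = 40 from 96% to 62% (two time points, correlation 0.5) or from 99% to 82% (three, 0.5). For two time points the corrected power runs from 41% to 91% as the correlation goes from 0.3 to 0.7. These figures assume that 0.30 is Cohen's f for a group-by-time interaction. The size of the power loss is therefore uncertain; the inflation of the error rate does not depend on it.

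**What to change.** Before any data are seen, name one primary outcome and one time point, chosen by the sponsor. Alpha then stays at 5%, and the sample-size statement applies to a named test. Make every other listed measure secondary. Either control error over that list with Holm or a false discovery rate procedure, or report estimates with confidence intervals and make no significance claims. Make the Abstract, the aims and the outcome sections list the same outcomes, and say where blood pressure, salivary IgA and lysozyme belong.

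The cost is more than rewording. The Ethics and dissemination section requires a formal amendment, agreed by the research team and approved by the ethics committee, for changes to study outcomes; the registry entry also has to be updated. Fewer nominally significant results could then be called primary. No added recruitment or measurement follows from naming one primary outcome.
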